## Abstract

**Background:**

Dupuytren’s contracture (DC) is a fibrotic hand condition in which one or more fingers develop progressive flexion deformities. Quality of life is diminished due to disabling limitations in performing everyday activities. For DC patients treated with collagenase, referral for subsequent hand therapy is inconsistent. It is unknown whether subsequent hand therapy is beneficial compared to no therapy. The purpose of this study is to determine whether hand therapy improves DC patients’ performance of and satisfaction with performing everyday activities one year after collagenase treatment.

**Methods:**

We will conduct a randomised controlled trial with two treatment groups (hand therapy vs. control) of DC patients who have received collagenase treatment. DC patients with contracted metacarpophalangeal joint(s) (MCPJ) (hand therapy, *n* = 40; control, n = 40) and those with proximal interphalangeal joint(s) (PIPJ) involvement (hand therapy, n = 40; control, n = 40) comprise two subgroups, and we will study if the treatment effect will be different between both groups (*n* = 160). Patients with a previous injury or treatment for DC in the treatment finger are excluded. Hand therapy includes oedema and scar management, splinting, movement exercises, and practice of everyday activities. The main outcome variable is patients’ performance of and satisfaction with performing everyday activities, as assessed with the Canadian Occupational Performance Measure. Secondary outcomes are DC-specific activity problems, as assessed with the Unité Rhumatologique des Affections de la Main scale, and active/passive flexion/extension of treated joints and grip force using standard measuring tools, and self-reported pain level. Demographic and clinical variables, degree of scarring, cold hypersensitivity, number of occupational sick-leave days are collected. Self-reported global impression of change will be used to assess patient satisfaction with change in hand function. Assessments are done pre-injection and 6 weeks, 4 months, and 1 year later. Standard univariate and multivariate statistical analyses will be used to evaluate group differences.

**Discussion:**

This study aims to assess whether hand therapy is beneficial for activity-related, biomechanical, and clinical outcomes in DC patients after collagenase treatment. The results will provide an objective basis for determining whether hand therapy should be conducted after collagenase treatment.

**Trial registration:**

This study has been registered at ClinicalTrials.gov as NCT03580213 (April 5, 2018).

## Background

Dupuytren’s contracture (DC), also known as Dupuytren’s disease, is a progressive fibroproliferative disorder affecting the palmar and digital fascia of the hand [1]. The development of nodules and cords in the palm may lead to flexion deformity and limitation of function [2, 3]. DC is autosomal dominant with variable penetrance. Prevalence estimates depend on geographic location, mail gender and increase with age [1]. In Sweden 56% of the diagnosed DC patients received treatment [4]. DC affects both performance of everyday activities and quality of life [5, 6]. The most disabling self-reported limitations in activity include difficulties in body washing and grooming, putting on gloves, shaking hands, and doing carpentry [6, 7].

Currently only symptomatic treatment exists for DC patients [8]. The only nonsurgical treatment approved in Europe is direct injection of collagenase clostridium histolytic (CCH) into a pathological cord [9]. CCH enzymatically dissolves collagen, allowing the contracted cords to be disrupted and eased by gentle force 1–2 days after injection [10]. CCH is an effective and safe treatment for DC, as shown in a five-year follow-up study [11]. CCH is considered to be successful when a treated joint can be extended to 0–5° of full extension and clinical improvement exceeds 50% reduction of the contracture [12]. Patients treated in our clinic with CCH for DC are treated with one injection in one to three fingers. If the skin is tight during the extension procedure two days later, a few also get a needle fasciotomy performed in the same procedure. It is up to the surgeon if the patient is referred for hand therapy or not within 1–2 weeks.

Inflammatory responses resulting from collagenases’ mechanism of action are reported, in addition to some complications; oedema, local contusions, scarring, haematoma, persistent joint contracture, pain, poor finger flexion, reduced grip strength, skin lesions, and tendon lesions [2, 13–17]. Patient satisfaction deteriorates with time if the contracture recurs [18, 19].

DC patients’ positive view of hand function after treatment is based on self-evaluation of whether their previous activity limitations have diminished [20]. It seems reasonable to hypothesize that hand therapy after CCH treatment might help to improve performance of these activities and temper other DC-related issues.

Hand therapy plays an important role in helping patients regain maximum function and minimizes further disability [13]. It is a symptom-based and clinically reasoned treatment that depends on an individual patient’s outcomes and circumstances [21, 22]. Recommendations for hand therapy after treatment for DC vary in the literature and in practice. Patient education, oedema management [23–25], wound care and scar management [26–28], splinting, exercises, passive stretching, and graded return to everyday activities are mentioned [13].

To our knowledge, the only study evaluating a post-CCH hand therapy protocol alone, relates to patients having a severely contracted proximal interphalangeal joint (PIPJ) [29]. In this case, hand function improved after 4 weeks of hand therapy following CCH treatment. However, lacking a control group, this protocol needs further evaluation, especially using long-term follow-up. In two other studies mentioning post-CCH treatment, DC patients wore a night splint, and in one study, patients also performed exercises [12, 30].

The primary goal of splinting for DC is to reduce the risk of recurrence and to prevent flexion contracture caused by scarring [31]. If the CCH treatment is unsuccessful, a splint might promote more joint extension [32, 33]. Targeted splinting for PIPJ contracture has produced good results after 4 weeks of splinting [29]. However, four systematic reviews all conclude that evidence in the literature does not support night splinting for DC post-surgery [21, 31, 34, 35]. It is clear from these studies, however, that compliance is important. No definitive conclusions can be made about the possibility that hand splinting might be beneficial post CCH. Reasons why patients discontinued using the splinting are many [22]. Optimal moulding of the splint, and the principle of applying low-grade force for longer periods of time, must be followed to produce tissue change without tissue micro-tears if the purpose of the splint is to straighten the joint further [32, 33].

With DC, ligaments and associated tissues have been in a shortened position for a period of time. To recover ROM, the patient’s finger ligaments and associated tissues needs to be elongated through finger exercise, use of the hand, and splinting. Exercises that maintain the metacarpophalangeal joint (MCPJ) in flexion, and at the same time, allow the PIPJ to be actively extended will improve PIPJ extension. In order to lengthen an oblique retinacular ligament that is frequently in a contracted or shortened condition, the PIPJ can be held in full extension, and the distal interphalangeal joint (DIPJ) can be exercised through active movement [32]. General hand exercises are necessary if the fingers have reduced function, as will general use of the hand in everyday activities.

In our literature search, no studies emerged that looked at the use of activities to improve function following CCH treatment. In a RCT on hand injury rehabilitation, patients with a hand injury improved more after an occupation-based intervention combined with exercises than when they performed exercises only [36]. Patients in the intervention group incorporated specific activities into their daily lives. Performing meaningful occupation-related tasks instead of rote exercises is critical for the efficacy of constraint-induced therapy following median and ulnar nerve injuries [37]. Overall hand function improved more when patients performed purposeful activities that mimicked typical everyday activities than when they performed exercises alone [38]. Performing purposeful activities accelerates the recovery of hand injuries, it also naturally increases the number of activity repetitions compared to engaging in non-purposeful activities [36]. Encouraging patients to use their affected hand more and more in everyday activities will also probably improve their actual performance of these activities and satisfaction with them.

In summary, no studies have compared the effects of hand therapy versus no therapy. Information about the effect of hand therapy post CCH is limited. As with other treatments, the body reacts to CCH treatment by invoking a healing process. Also, patients seek to improve activity performance. In this study we want to investigate if hand therapy amplify the healing process to prevent re-contracture and improve the patients’ performance of and satisfaction with everyday activities.

## Methods/design

### Aims

The main purpose of this study is to determine whether hand therapy administered following CCH treatment for DC improves patients’ performance of and satisfaction with performance of their everyday activities 1 year after CCH treatment. The comparison group will not receive hand therapy following CCH treatment for DC. In addition, this intervention will be evaluated in cases involving PIPJ contractions versus cases involving only MCPJ contractions.

### Hypotheses

H1. After CCH treatment for DC, patients who receive hand therapy will improve their performance of everyday activities more than those patients who do not receive hand therapy.H2. After CCH treatment for DC, patients who receive hand therapy will be more satisfied with their performance of everyday activities than those patients who do not receive hand therapy.H3. Involvement of the PIPJ in the DC is a better predictor for improvement after receiving hand therapy than involvement of only the MCPJ.H4**.** The treatment effect (hand therapy vs. control) for the COPM will be greater for patients where PIPJ is involved than for that where MCPJ solely is involved

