### Statistical analysis

We determined the appropriate sample size according to the minimal clinically important change for the COPM [44]. COPM gives two main outcomes; performance of activity, and satisfaction with performance. There is strong correlation between the two [60], and we therefore used both for the calculation of the sample size. Van de Ven-Stevens reported a standard deviation (SD) of 1.1 for performance and 0.8 for satisfaction for DC patients assessed with the COPM [47]. For this trial, we assumed a more conservative value, setting the SD to 2.0. For our power analysis, we conservatively assumed we would detect an effect only in the PIPJ group, which would produce a mean COPM difference of 1.0 between the hand therapy and control groups. Power analysis shows that we require 64 participants in each group to detect this difference for a two-sided t-test, with a significance level of *p* < 0.05 and power of 0.8. These parameters suggest we need 32 patients in each PIPJ and MCPJ subgroup. This would enable us to detect a mean difference of 2.0 (SD = 2) between PIPJ and MCPJ in the intervention group, with a power of 0.98. Assuming 20% loss-to-follow-up [22], we require 80 patients in the no hand therapy group and 80 in the hand therapy group.

Descriptive statistics will be used to characterise the participants’ data at baseline and follow-ups, and separately for the data of those participants who might drop out from the study. The baseline values of every measure will also be used to describe the randomised groups to determine their comparability.

The effect of post-CCH hand therapy at 1 year will be assessed using analysis of covariance (ANCOVA). The development of changes over time will be evaluated using a linear mixed-effects model, with time, intervention group, and their interaction as predictors. An intention-to-treat analysis will be used. The predictive value of PIPJ/MCPJ will be assessed by adding the interaction between group and PIPJ/MCPJ to the models. Results will be summarised by graphical illustrations.

The significance level is set to *p* < 0.05. SPSS and Matlab® (MATLAB and Statistics Toolbox Release 2012b, The MathWorks, Inc., Natick, MA, USA) will be used for statistical analyses and creation of Figures.

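### The protocol powers PIPJ against MCPJ-only within the therapy arm (H3) but names only the group by joint-type interaction (H4) as its test

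*Protocol article*

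**What the plan says.** The Hypotheses section of the protocol article lists two separate statements about joint type.

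- H3: "Involvement of the PIPJ in the DC is a better predictor for improvement after receiving hand therapy than involvement of only the MCPJ". As worded, it concerns patients who received therapy and has no control term.
- H4: "The treatment effect (hand therapy vs. control) for the COPM will be greater for patients where PIPJ is involved" than for patients with MCPJ involvement alone. This is a difference between two treatment effects.

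The Statistical analysis section then does two things.

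- It gives one analysis for joint type: "The predictive value of PIPJ/MCPJ will be assessed by adding the interaction between group and PIPJ/MCPJ to the models". The models are the 1-year ANCOVA and the linear mixed model.
- It gives one power figure for joint type. After "These parameters suggest we need 32 patients in each PIPJ and MCPJ subgroup", it says that this number allows the trial to "detect a mean difference of 2.0 (SD = 2) between PIPJ and MCPJ in the intervention group, with a power of 0.98".

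The Design section adds only that differences will be evaluated among the four subgroups. It does not assign a contrast to either hypothesis.

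**The concern.** The contrast that is powered and the contrast that is named for testing are different quantities. H3's wording and the 0.98 sentence point to a comparison of joint types inside the therapy arm. The interaction compares the therapy-control difference in PIPJ patients with the same difference in MCPJ-only patients.

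Two things are at stake. First, a significant interaction could be reported as support for H3 when treated PIPJ and MCPJ-only patients improved equally, because the interaction also depends on what happens in the control arm. Secondly, a reader of the sample-size paragraph will credit the joint-type question with power of 0.98, although the named test does not have it. The Discussion says that the results should inform referral policy. For that purpose the treatment effect by joint type (H4) is the relevant quantity, so it should be clear which result answers which question.

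**Working it through.** **Inputs, all from Statistical analysis.** SD: "For this trial, we assumed a more conservative value, setting the SD to 2.0". Effect: "we would detect an effect only in the PIPJ group, which would produce a mean COPM difference of 1.0". Arm size: "we require 64 participants in each group to detect this difference for a two-sided t-test". There are 32 per cell, two-sided alpha is 0.05, and 20% loss is allowed for.

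**The plan's own figures reproduce.**
- Arms: SE = 2 × √(2/64) = 0.354 and 1.0/0.354 = 2.83. The t-test has power 0.801, against the stated 0.8. Allowing for loss, 64/0.80 = 80 per arm.
- PIPJ against MCPJ-only within the therapy arm: SE = 2 × √(2/32) = 0.50 and 2.0/0.50 = 4.0. Power is 0.979 by normal approximation and 0.976 by noncentral t (62 df), against the stated 0.98.

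**The named test.** The interaction has SE = 2 × √(4/32) = 0.707.
- For 2.0 points: 2.0/0.707 = 2.83, power 0.801 (124 df).
- For 1.0 point: 1.0/0.707 = 1.41, power 0.289.
- With no loss at all (40 per cell), power for 2.0 points is 0.88.
- For power 0.98 at 2.0 points: n per cell = 4 × [2 × (1.960 + 2.054)/2]² ≈ 64.4, so 65, about twice the planned 32.

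**How the two contrasts relate.** Let T be PIPJ minus MCPJ-only mean improvement in the therapy arm, and C the same difference in the control arm. H3 as worded concerns T. The interaction is T − C. Hence the nulls T = 0 and T − C = 0 coincide only when C = 0.

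In the planning case the effect is confined to PIPJ. With equal subgroups, (2.0 + 0)/2 = 1.0, so the PIPJ effect is 2.0 and the interaction is 2.0. T is also 2.0, but only if the control subgroups are equal. Even then the powers differ: 0.80 for the interaction and 0.98 within the arm.

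**Illustration.** The protocol gives no cell means, so these are assumed. Each row is 40,000 simulated trials with 32 per cell and SD 2.0; the within-arm test uses the four-cell pooled variance.

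| Therapy PIPJ, MCPJ | Control PIPJ, MCPJ | T | T − C | Interaction rejects | Within-arm test rejects |
|---|---|---|---|---|---|
| 2, 2 | 1, 2 | 0 | 1.0 | 0.289 | 0.050 |
| 2, 2 | 0, 2 | 0 | 2.0 | 0.799 | 0.048 |
| 4, 2 | 3, 1 | 2.0 | 0 | 0.047 | 0.979 |
| 4, 2 | 2, 2 | 2.0 | 2.0 | 0.801 | 0.978 |

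Rows 1 and 2 are correct detections for H4. They would be false support only if read as answering H3 as worded. Row 3 is the reverse: a purely prognostic difference that the interaction rightly ignores.

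**The case against.** The strongest reply is that H3 was meant as effect modification. A predictive factor in trial usage is one that changes the treatment effect, the interaction is the standard test for it, and the Aims section frames the joint question as an evaluation of the intervention in the two kinds of case. The wording of H3 is loose enough to allow this, since PIPJ-involved and MCPJ-only are two levels of one stratification factor. On this reading the test is right. What remains is that H3 repeats H4 and that the 0.98 sentence describes a contrast answering neither.

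It can also be said that a model with the joint main effect and the interaction already yields the within-arm contrast, and that mapping contrasts to hypotheses is often left to an analysis plan, which is not shown here. The first part is true and makes the remedy easy. The second does not settle the matter, because the article itself fixes the hypotheses, the analysis and the power, and these do not agree.

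A reader might infer more: that the trial will declare H3 supported wrongly at these rates, or that it loses most of its power for H3 (5% against 98% in row 3 of the table). The documents do not support either. The rates depend on control-subgroup means that the protocol does not give, and the Statistical analysis section does not tie the interaction to a numbered hypothesis. A lower chance of detecting a purely prognostic difference is no loss for the question of who benefits from therapy. Nor does it follow that H3 should simply be deleted: that alone would leave the 0.98 statement attached to no planned inference.

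**Conclusion.** The mismatch holds under either reading of H3. If H3 is a comparison among treated patients, it is powered but has no named test. If H3 is effect modification, it duplicates H4 and the power sentence refers to the wrong contrast. The firm figure is the power: about 0.80, not 0.98, for an interaction of 2.0 points with 32 per cell, and about 0.29 for 1.0 point.

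These figures take the protocol's SD of 2.0 as the SD of the analysed outcome. Baseline adjustment would lower the residual SD and raise both powers, but it would not make the two nulls the same. The 29% and 80% rejection rates illustrate the logic under assumed means; they do not estimate this trial's error rate. H1, H2 and the specification of H4's own test stand. The point affects what may be concluded about joint type, and it should be corrected before analysis.

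**What to change.** 1. Name the 1-year group by PIPJ/MCPJ interaction as the single inferential test of joint type, under H4. Replace the sentence "The predictive value of PIPJ/MCPJ will be assessed by adding the interaction between group and PIPJ/MCPJ to the models" with one saying that this interaction estimates the difference in treatment effect between PIPJ and MCPJ-only patients.
2. Either merge H3 into H4, or keep H3 as a prognostic, non-randomised contrast within the therapy arm. In the second case take it from the same model (joint main effect plus interaction, with control as reference), report it with a 95% confidence interval beside the matching control-arm contrast, and state that it is not evidence of benefit from therapy.
3. Give power by contrast: about 0.80 for an interaction of 2.0 points with 32 per cell, with 0.98 applying only to the within-arm contrast.

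The cost is a less favourable stated power for joint type and one fewer causal hypothesis. No new data, model or patients are needed.

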### Design

The possible benefits of hand therapy on the participants’ performance and satisfaction with performing their everyday activities will be investigated in addition to range of motion. A randomised controlled trial with two groups will be used (Fig. 1). One group will receive hand therapy after CCH treatment, and the other group will not. Participants will be randomly allocated into the two groups. Additionally, the two groups each have two equally sized subgroups: one with PIPJ involvement (MCPJ and PIPJ or PIPJ only), and the other with only MCPJ involvement. Thus, there will be four groups, (“MCPJ and PIPJ or PIPJ only” / “MCPJ only”) x group type (hand therapy/control) (Fig. 1). Differences on actual performance of activities and satisfaction with that performance, before and after hand therapy or not, will be evaluated among the four subgroups.

**Fig. 1 Fig1:**
[figure not shown]
Flow chart illustrating the selection, allocation, intervention, and assessment schedule of patients with Dupuytren’s contracture**.**
^a^ Reasons for receiving hand therapy after allocation to the control group are developing CRPS or an infection. This will be noted and considered in the analysis

### Setting of the study

The Department of Occupational Therapy, Orthopaedic Clinic, Haukeland University Hospital (HUH) will oversee the study and will be ultimately responsible for conducting the study and results. Some participants may live far away from the treatment location, as the HUH serves a large geographical area around Bergen. The intervention will be carried out in an outpatient clinic at the hospital.

### Participants

This study is currently recruiting participants (study start date: 10th of April 2018). Adult men and women who have had their DC treated with one CCH injection in one-tree fingers with joints summarised to ≥30° extension deficit are eligible. Patients can participate only once. Reasons for exclusion are as follows:
having previous treatment for DC in the same finger being considered for the interventionhaving previous surgery or a major injury that affects the same fingers movementhaving complex regional pain syndrome, infection, or an allergic reaction to the CCH before randomisationhaving a tendon or ligament rupture in the hands before randomisationa patient incapable of complying with a therapy program due to cognitive or language challenges.

Activity performance and satisfaction are affected by capacity of both hands. Therefore, participation in the study is appropriate only once. If any of the included participants receive DC treatment in the unparticipating hand, or for other fingers of the experimental hand, during the present trial, this will be noted and considered as an adjustment variable in the analysis. Previous injury or DC treatment would undoubtedly cause changes in the connective tissue and would likely confound the results of our study. Participants who develop complex regional pain syndrome (CRPS) or infection, diagnosed by a doctor, must undergo hand therapy regardless of whether it affects hand function severely. This will be considered in the analysis as an adjustment variable.

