#### Control group

Participants in the control group are discharged from hospital without further interventions, not even a post-treatment appointment with the surgeon. The participants in this group are neither informed of what exercises to do, nor are they to be fitted for a splint or cast. If an infection is detected or CRPS diagnosed by the personal general practitioner or the surgeon, treatment accordingly (most often hand therapy) will be initiated. The Budapest criteria for CRPS will be used [40]. If not diagnosed when meeting at the 6 weeks or 4 months re-tests, the tester will contact a MD to do it. If CRPS develops, this participant will be marked as treated with a deviation from the protocol (Fig. 1). This marking will also be done if it is revealed that a participant has received some kind of hand therapy outside of the hospital.

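### Two events that arise after randomisation are named as adjustment variables and are not kept out of the primary models, so the adjusted group coefficient can depart from the effect of assignment

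*Protocol article*

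**What the plan says.** All references are to the protocol article.

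- **Participants, further Dupuytren's treatment.** Treatment of the non-study hand, or of other fingers of the study hand, is to be handled as follows: "during the present trial, this will be noted and considered as an adjustment variable in the analysis".
- **Participants, CRPS or infection.** "Participants who develop complex regional pain syndrome (CRPS) or infection, diagnosed by a doctor, must undergo hand therapy", and then: "This will be considered in the analysis as an adjustment variable". The same section excludes anyone with CRPS or infection before randomisation, so the cases to be adjusted for can only arise afterwards.
- **Fig. 1 footnote.** "Reasons for receiving hand therapy after allocation to the control group are developing CRPS or an infection". The footnote says this will be noted and considered in the analysis, without saying how.
- **Control group.** "If CRPS develops, this participant will be marked as treated with a deviation from the protocol". Hand therapy obtained outside the hospital is marked in the same way.
- **Statistical analysis.** "The effect of post-CCH hand therapy at 1 year will be assessed using analysis of covariance (ANCOVA"). A mixed model has time, group and their interaction as predictors, and the group-by-joint interaction is added to the models. "An intention-to-treat analysis will be used". The two events are neither listed as covariates here nor assigned to a sensitivity analysis.
- **Intervention (all participants).** Needle fasciotomy is also an adjustment variable. It belongs to the extension procedure, and the Randomisation and blinding section has the envelope opened only when collagenase treatment is finished. It therefore precedes allocation and raises no problem.

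**The concern.** A covariate measured before allocation cannot be changed by allocation, so adjusting for it leaves the meaning of the group coefficient intact. A covariate that arises afterwards has no such protection. If allocation changes how often the event occurs, adjustment removes the part of the effect that runs through the event. If the event also shares unmeasured causes with the outcome, such as poor healing, adjustment compares groups that are no longer alike in prognosis.

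Three features make this more than a formality for CRPS/infection:

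- The variable means different things in the two arms. In controls it brings in the experimental treatment; in the therapy arm it marks only a complication. Adjusting for it partly adjusts for crossover, which an effect of assignment should leave in.
- Hand therapy could plausibly alter how often these complications occur.
- Recording may differ by arm. Controls have no post-treatment appointment with the surgeon, while therapy participants have at least three sessions by 6 weeks and free access to the therapist.

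For further Dupuytren's treatment, the Participants section itself notes that activity performance depends on both hands, so the variable bears on the COPM. Its route from allocation is weaker.

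At stake is the question that the trial is meant to inform, whether to refer patients for hand therapy after collagenase. That is a question about the effect of assignment.

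**Working it through.** **1. The plan's own figure.** Inputs from Statistical analysis: difference 1.0, SD 2.0, two-sided 5% level, power 0.8, 20% loss. The t-test calculation gives 63.77, so 64 per group (power 0.801), and 64/(1 - 0.2) = 80. Both stated figures reproduce. Nothing below changes them.

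**2. Precision.** With 64 per group analysed, the standard error of the difference is 2.0 × √(2/64) = 0.354 COPM points.

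**3. What adjustment does to the coefficient.** Let p_C and p_T be the event proportions in the control and therapy arms, and b_M the fitted coefficient of the event. For least squares with group and event as predictors,

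unadjusted coefficient = adjusted coefficient + b_M × (p_T - p_C),

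so shift = adjusted - unadjusted = b_M × (p_C - p_T).

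The shift is zero when the event rates are equal and changes sign when the imbalance reverses.

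**4. A value for b_M (assumptions, not from the documents).** An unmeasured prognostic factor U (standard normal) correlates 0.6 with the liability to the event and has outcome coefficient -1. The direct effect of therapy is 1.0 and the total SD about 2. The event itself changes the 1-year COPM by e, from 0 to -2 points. Then b_M = e - D, where D is the within-arm difference in mean U between participants with and without the event:

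D = 0.6 × [φ(z_C) + φ(z_T)] / [p_C(1 - p_C) + p_T(1 - p_T)],

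with φ(z) the normal density at the threshold that cuts off the stated proportion.

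Worked case, 10% versus 5%: D = 0.6 × (0.1755 + 0.1031)/(0.0900 + 0.0475) = 1.216. With e = 0 the shift is -1.216 × 0.05 = -0.06. With e = -2 it is -3.216 × 0.05 = -0.16.

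| Event rate, control vs therapy | D | Shift, e = 0 | Shift, e = -2 | Largest shift / 0.354 |
|---|---|---|---|---|
| 3% vs 3% | 1.403 | 0.00 | 0.00 | 0 |
| 5% vs 2% | 1.355 | -0.04 | -0.10 | 0.28 |
| 10% vs 5% | 1.216 | -0.06 | -0.16 | 0.45 |
| 20% vs 10% | 1.093 | -0.11 | -0.31 | 0.88 |
| 5% vs 10% | 1.216 | +0.06 | +0.16 | 0.45 |

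A simulation of the same model (10 runs of 200,000 patients per scenario) agrees. At 20% versus 10% with e = -2, the unadjusted coefficient was 1.197 and the adjusted one 0.891, a difference of -0.306.

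**5. Scale in patients.** With 64 per arm, 5% versus 2% is about 3 versus 1 participants (3.2 and 1.3), 10% versus 5% about 6 versus 3, and 20% versus 10% about 13 versus 6.

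**The case against.** Four points can fairly be made for the plan.

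- **Placement is not stated.** The Participants section says only that the events will be considered as adjustment variables. The models in Statistical analysis do not list them, the Fig. 1 footnote does not mention adjustment, and marking controls as deviations would fit a sensitivity or per-protocol analysis. This stands: a reader might infer that the primary ANCOVA will contain these covariates, but the text does not say so. It does not rule it out either, which leaves the choice open until the data are seen.
- **Intention-to-treat is not breached as an analysis set.** A reader might infer a contradiction between the two sections. Nothing in the article removes participants or moves them to the other arm. The tension is only between an adjusted coefficient and the effect of assignment that such an analysis is meant to estimate. This stands.
- **Bias needs imbalance.** With equal rates the shift is nil. Splinting, scar care and exercise for the treated hand have no evident route to treatment of the other hand, and indications for treatment elsewhere are recorded at baseline. Testers also check for CRPS in controls at 6 weeks and 4 months, which limits differential detection. This stands as a reason to centre the point on CRPS/infection. It does not justify naming either event as a covariate.
- **The larger shifts need severe inputs.** The 20% versus 10% case with e = -2 supposes a loss equal to the full change that the article deems clinically important. A reader might go further and infer that adjustment could reverse the sign. With those inputs and no direct effect, +0.20 does become about -0.11, but the documents support neither the rates nor the absence of a direct effect.

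**Conclusion.** The concern holds in a conditional form. The article names two post-randomisation events as adjustment variables and does not keep them out of the primary models. If they enter, the group coefficient can depart from the effect of assignment, most plausibly through CRPS/infection.

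Neither size nor direction can be settled from the article, because it gives no event rates. At 5% versus 2% up to 10% versus 5%, the shift is 0.04 to 0.16 COPM points, less than half of the 0.35 standard error. At 20% versus 10% it reaches 0.31, close to one standard error. These figures rest on the assumed link between prognosis and event and on an event effect of 0 to -2 points. The documents do not support the statement that the main result will be biased. They do contain a stated analysis rule that can distort it and is easily corrected.

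**What to change.** In Participants, replace both statements about adjustment variables, and in Statistical analysis add text to this effect:

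> The 1-year ANCOVA and the mixed model adjust only for variables fixed before randomisation: baseline COPM, PIPJ/MCPJ stratum and needle fasciotomy. All participants are analysed in the arm to which they were allocated, whether or not they develop CRPS or infection, receive hand therapy as controls, or have Dupuytren's treatment elsewhere during follow-up. These events are tabulated by arm. Any analysis that takes them into account is labelled as a sensitivity analysis.

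In the Fig. 1 footnote, point to the tabulation and the sensitivity analysis, so that all places describe the same handling. The marking of deviations in the control group can stay.

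The cost is a few sentences, one table and one sensitivity analysis. Sample size, data collection and the clinical handling of CRPS and infection are unaffected.
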